### Outcomes

#### Primary outcome

The primary outcome of our study is the difference between the index group and control group on all measures of subjective (daily self-assessment questionnaires) and objective (ActTrust measurements, sleep onset latency, sleep efficiency, WASO and awakenings) sleep quality, the pattern of the CAR and the course of alpha-amylase after awakening.

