#### *A priori* power calculation

*A priori* sample size was calculated with the program G*Power version 3.1.9.4,^61^ based on a previous study by Schmidt et al^14^ with a medium effect size of *f* = 0.30, an *α* error probability of 0.05 and two groups. To investigate group differences in the CAR through a repeated measures analysis of covariance (ANCOVA), a total of 28 participants would be required to achieve a power of 80%. In accordance with Selvi et al, we assume a medium effect size of *d* = 0.40 for correlational analyses of sleep quality and depressive symptoms.^62^ A sample size of *N* = 44 was deemed necessary for statistical power of 80%. Finally, to enable the calculation of a direction-dependence analysis in case of non-normally distributed and sufficiently skewed data,^63^ we will include a sample of *N* = 60 participants: 30 participants with a depressive disorder and 30 healthy participants as parallel controls.

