### Statistical analysis

Data will be collected in accordance with the current standard of empirical research. Data will be evaluated with IBM SPSS Statistics version 25.0 for Windows (released 2017; IBM Corp, Armonk, New York). First, depending on the distribution of control variables, differences between the adolescents with depression and the control group will be computed via *t*-tests or Mann–Whitney *U*-tests. As cortisol and alpha-amylase levels are commonly skewed, a square-root transformation will be applied to achieve a normal distribution.^64^ Cortisol and alpha-amylase measurements will be averaged over three days and entered into the repeated measures ANCOVA as the dependent variable, with group as the independent variable.

Cortisol and alpha-amylase increase will be computed by area under the curve analyses.^65^ For an additional measure of increase, delta scores will be computed between baseline and the highest value.^66,67^ To determine group differences in cortisol and alpha-amylase increase, ANCOVAs will be calculated with group as an independent variable.

To examine the relationship between subjective and objective sleep quality, depressive symptoms and cortisol/alpha-amylase increase, bivariate correlations with a false discovery rate correction will be computed.^68^ Effect sizes will be reported with Cohen's *d*, with 0.2 being considered a small, 0.5 a medium and 0.8 a large effect.

Finally, in case of non-normality distributed and sufficiently skewed outcome variables, the direction of the relationship between sleep quality and depressive symptoms will be examined with direction dependence analysis.^63^ Direction dependence analysis enables to statistically test the directional relation between pairs of variables, including observational variables, as well as adjusting for covariates that may contribute to the causal process.^69^

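### Many measures are jointly primary with no hierarchy, and the only stated multiplicity correction covers the correlations, not the primary group comparisons

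*Protocol article*

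**What the plan says.** The Primary outcome section of the protocol article reads: "The primary outcome of our study is the difference between the index group and control group on all measures of subjective" and objective sleep quality. The subjective side is the daily self-assessment questionnaires. The objective side is four accelerometer measures: onset latency, efficiency, wakefulness after sleep onset and awakenings. The cortisol awakening response (CAR) and the alpha-amylase course are added. Nothing ranks these or says what combination of results would count as success.

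The Hypotheses section names five subjective aspects, each with a predicted direction: satisfaction, mood, recreation, awakenings and dreams. The Daily sleep questionnaires section describes 11 items and defines no combined score.

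The Statistical analysis section plans a repeated-measures ANCOVA for cortisol and alpha-amylase. It then turns to area under the curve (AUC) and delta scores: "To determine group differences in cortisol and alpha-amylase increase, ANCOVAs will be calculated with group as an independent variable". Multiplicity appears once, for the associations between sleep, symptoms and biomarkers: "bivariate correlations with a false discovery rate correction will be computed".

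A significance level appears only in the power calculation: "error probability of 0.05 and two groups".

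**The concern.** When several comparisons share primary status and no rule links them, any one significant result can be reported as the primary finding, and a mixed pattern has no agreed meaning. The authors considered multiplicity and chose a method for it, but attached it to the correlations. The comparisons that carry the study's main claims are left outside it. If the text is followed literally, the risk of a spurious primary difference is well above the nominal 5%.

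**Working it through.** **The plan's own figures.** The article states no family-wise error rate, so there is none to reproduce. Its sample sizes (28 for the CAR, 44 for the correlations, 60 finally) do not bear on the error rate. The 28 cannot be judged right or wrong, because the correlation among repeated samples and the effect tested are not given.

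**Inputs**
- Alpha 0.05: A priori power calculation. Using it for each group comparison is an assumption.
- Objective sleep measures: 4 (Primary outcome).
- Subjective aspects: 5 (Hypotheses). Testing them separately is an assumption; one composite would count as 1.
- Biomarkers: 2 (Primary outcome), one repeated-measures test each.

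**Count.** 4 + 5 + 2 = 11 tests. With one subjective composite, 4 + 1 + 2 = 7.

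**Independent tests, all nulls true.** P(at least one false positive) = 1 − (1 − 0.05)^k.
- k = 11: 1 − 0.95^11 = 0.431
- k = 7: 1 − 0.95^7 = 0.302

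**Correlated tests.** Measures such as efficiency and wakefulness after sleep onset are linked, so independence overstates the risk. The article gives no correlations, so the values below are assumed. Eleven two-sided z-tests were simulated with 200,000 draws.

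| Assumed correlation among the 11 tests | P(at least one false positive) |
|---|---|
| Common, 0.2 | 40% |
| Common, 0.3 | 38% |
| Common, 0.5 | 30% |
| Common, 0.7 | 22% |
| Blocks: 0.3–0.7 within each sleep domain, 0.1–0.3 between them, biomarkers independent | 33–41% |

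**Some effects real.** If all five subjective differences exist, 11 − 5 = 6 nulls remain: 1 − 0.95^6 = 0.265 under independence.

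**Predicted direction only.** If only a result in the hypothesised direction counts, each two-sided 5% test contributes 2.5%: 1 − 0.975^11 = 0.243 under independence.

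**Power cost of correcting.** With 30 per group and a standardised difference of 0.8, power for one comparison is 86% at 0.05. At the Bonferroni level for 11 tests, 0.05/11 = 0.00455, it is 56%. Bonferroni is used here only as a strict benchmark.

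**The case against.** This is a condensed article about a single-centre, non-interventional study of 60 adolescents. It never claims confirmatory error control, and the full plan is not shown. A correction named for the correlations does not exclude one elsewhere. Three stronger readings are tempting, and the text supports none of them.

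- **A reader might infer that at least 11 comparisons are each tested at 5%.** Eleven is not a minimum, since the article does not say whether questionnaire items are combined. The 5% level is stated only for the power calculation.
- **A reader might infer a false-positive risk of around 50%.** Adding AUC and delta for both biomarkers gives 15 tests and 1 − 0.95^15 = 54% if independent. But the primary outcome is the pattern of the CAR and the alpha-amylase course, which matches the repeated-measures ANCOVA. AUC and delta describe the increase, and delta is introduced as an additional measure of it.
- **A reader might infer that the study was sized for one cortisol test, which should therefore be the sole primary.** The power section also sizes the correlations and sets the final 60 for direction dependence analysis. It never says that group-by-time was the effect sized, and the Study aim section puts sleep quality first.

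That the article names no specific test for the sleep differences is a detail commonly left to an analysis plan, and is not part of this point.

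What stands of the objection is that the exact size is uncertain and that the choice of a primary belongs to the sponsor. It does not remove the defect. The article itself fixes a joint primary outcome with no hierarchy and itself places the correction on a different set of analyses.

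**Conclusion.** The point holds in a limited form. The primary outcome is a family of unranked comparisons, and the stated multiplicity correction does not reach it. Assuming 5% per test and all nulls true, the chance of at least one false-positive primary result is 43% for 11 independent tests, about 30–41% for 11 under moderate correlation, and 30% for 7 independent tests. If the subjective differences are real it is about 26%. Even a common correlation of 0.7 leaves 22%. No single figure can be asserted, because the number of tests, their level and their correlation are not stated. Every scenario examined is well above 5%.

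**What to change.** State before analysis that the false discovery rate procedure already planned for the correlations will also be applied to the full family of primary group comparisons: the objective sleep measures, the subjective sleep measures, and the repeated-measures tests for cortisol and alpha-amylase. List the members, and say whether the subjective items enter singly or as a composite. Label the AUC and delta analyses supportive.

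Alternatively, the sponsor may name one primary comparison in line with the Study aim section and apply the procedure to the rest. It need not be cortisol.

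The change takes a few sentences. Its costs are adjusted p-values and somewhat lower power per comparison. The loss from 86% to 56% shown above is for Bonferroni; a step-up procedure such as Benjamini–Hochberg rejects at least whatever Bonferroni rejects, so it would lose no more than that. A false discovery rate bounds the expected share of false findings among those declared. It does not bound the chance of any false finding once some effects are real, and the report should say so.

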#### Secondary outcome

The secondary outcome of our study is the examination of the severity of depressive symptoms, further psychopathologies, and stress responsiveness at the first study appointment and its relation to sleep quality.

#### *A priori* power calculation

*A priori* sample size was calculated with the program G*Power version 3.1.9.4,^61^ based on a previous study by Schmidt et al^14^ with a medium effect size of *f* = 0.30, an *α* error probability of 0.05 and two groups. To investigate group differences in the CAR through a repeated measures analysis of covariance (ANCOVA), a total of 28 participants would be required to achieve a power of 80%. In accordance with Selvi et al, we assume a medium effect size of *d* = 0.40 for correlational analyses of sleep quality and depressive symptoms.^62^ A sample size of *N* = 44 was deemed necessary for statistical power of 80%. Finally, to enable the calculation of a direction-dependence analysis in case of non-normally distributed and sufficiently skewed data,^63^ we will include a sample of *N* = 60 participants: 30 participants with a depressive disorder and 30 healthy participants as parallel controls.

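### The power calculation pairs d = 0.40 with N = 44 for 80% power, but N = 44 follows from a correlation of r = 0.40; the metric needs confirming and the paragraph restating

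*Protocol article*

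**What the plan says.** The section on the a priori power calculation (Protocol article) gives three steps. The first, for the cortisol awakening response, uses "an *α* error probability of 0.05 and two groups". The second concerns the link between sleep quality and depressive symptoms: "we assume a medium effect size of *d* = 0.40 for correlational analyses of sleep quality and depressive symptoms". It continues: "A sample size of *N* = 44 was deemed necessary for statistical power of 80"%. The third raises the total to 60, that is "30 participants with a depressive disorder and 30 healthy participants as parallel controls", so that a direction-dependence analysis is possible.

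The Statistical analysis section says how the second question will be tested: "bivariate correlations with a false discovery rate correction will be computed". It then names Cohen's d as the effect-size measure, "with 0.2 being considered a small, 0.5 a medium and 0.8 a large effect".

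The second step restates neither alpha nor sidedness, and does not name the G*Power test. Nowhere is 0.40 given as a correlation coefficient.

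**The concern.** Cohen's d measures a difference between two group means; a bivariate correlation is planned in terms of r. The two scales are far apart: the same 0.40 is a much stronger association as r than as d. A sample size derived on one scale cannot be reported on the other.

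The relation of depressive symptoms to sleep quality is the stated secondary outcome. A reader who takes the paragraph at its word will believe that the study can detect d = 0.40 with at least 80% power, and could read a null correlation as evidence against an effect of that size. If d = 0.40 really is the target, the study cannot provide that evidence.

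**Working it through.** **Inputs.** Effect 0.40, N = 44, power 80% and total N = 60 in a 30:30 split come from the power section. Alpha 0.05 is stated there for the first step and is assumed to carry over. Two-sided testing is assumed; one-sided results are also shown.

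**Formula.** Test of a correlation by noncentral t with N − 2 degrees of freedom and noncentrality λ = √(N·r²/(1 − r²)). Power is the probability that |t| exceeds its two-sided critical value.

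**1. Reproducing N = 44 with 0.40 read as r.**
- N = 43: λ = √(43 × 0.16/0.84) = 2.862, critical t = 2.020, power 79.8%.
- N = 44: λ = √(44 × 0.16/0.84) = 2.895, critical t = 2.018, power 80.7%.

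So 44 is the smallest N that reaches 80%. The exact bivariate-normal test gives 46 and Fisher's z gives 47, both close. One-sided, the three methods give 34 to 38, which does not match.

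**2. The effect as printed, d = 0.40.** With equal groups, r = d/√(d² + 4) = 0.40/√4.16 = 0.196.

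| Method | Total N for 80%, two-sided | One-sided |
|---|---|---|
| Two-sample t | 200 (100 per group) | 156 |
| Noncentral t, r = 0.196 | 199 | 156 |
| Exact bivariate normal | 201 | 159 |
| Fisher's z | 202 | 160 |

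Other readings do not give 44 either. A one-sample or paired t-test with d = 0.40 needs 52 (two-sided) or 41 (one-sided), and a two-group ANOVA with f = 0.40 needs 52.

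**3. Power at the two sample sizes (two-sided 0.05, one test, noncentral t).**

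| True effect | N = 44 | N = 60 |
|---|---|---|
| r = 0.40 | 80.7% | 91.4% |
| d = 0.40 (r = 0.196) | 25.4% | 33.2% |

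One-sided, d = 0.40 gives about 37% and 45%. The exact bivariate-normal test for r = 0.40 gives 78.4% and 89.7%.

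**4. Smallest correlation with 80% power at N = 60.** r = 0.345 gives 79.9% and r = 0.35 gives 81.2%, so about 0.35.

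**5. Effect of the false discovery rate correction.** The number of correlations is not given, so a range is assumed. In a step-up procedure the threshold for a given test lies between 0.05/m and 0.05. At the strictest step, for r = 0.40 and N = 60:

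| Assumed tests m | Threshold | Power |
|---|---|---|
| 2 | 0.0250 | 86% |
| 9 | 0.0056 | 69% |
| 27 | 0.0019 | 55% |

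These values are a floor. The expected power lies between them and 91%, depending on how many other correlations are real.

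**The case against.** The strongest reply is that this is one wrong symbol. The sentence is about correlational analyses, the analysis section plans bivariate correlations, and r = 0.40 returns exactly 44 while no standard calculation with d = 0.40 does. On that reading the sample size is right and N = 60 is comfortable for a single test. Moreover, N = 44 does not set enrolment, and the outcome concerned is secondary. All of this stands, and it limits the weight of the point.

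A reader might infer that the study has only one-third power for its secondary question. The documents do not support that: the 33% holds only if d = 0.40 was truly intended, which is the less likely reading. A reader might also infer that r = 0.40 is a large effect on the article's own scale, since it converts to d = 2 × 0.40/√(1 − 0.16) = 0.87. That conversion assumes two equal groups, whereas depressive symptoms are measured by a questionnaire score, so it is not the natural comparison. Calling 0.40 medium when the reporting scale puts medium at 0.5 is loose wording and no more. Nor do the documents support a single low power figure after correction, because they do not give the number of tests and the strictest step is only a bound.

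What the reply does not remove is that the printed effect, sample size and power cannot all be true. A condensed article may leave out detail, but no fuller document can make these three figures agree.

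**Conclusion.** The paragraph is wrong as printed. With d = 0.40 the study would need about 199 to 200 participants (156 to 160 one-sided) rather than 44, and would have about 25% power at 44 and 33% at 60. With r = 0.40, N = 44 is correct and N = 60 gives about 91% for one uncorrected test. The incompatibility does not depend on sidedness or on the choice of test; the exact figures assume two-sided alpha 0.05, and the conversion from d to r assumes equal groups. A mislabelled metric is the likeliest explanation, but the source cited for the effect size is not at hand, so only the authors can confirm it. This is a should-fix: a false planning statement about a named secondary outcome, without consequence for enrolment.

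**What to change.** Confirm which metric was used in the calculation, then restate the paragraph.

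- **If r was meant:** remove d = 0.40 and write, for example: *assumed correlation r = 0.40; N = 44 for 80% power, two-sided alpha 0.05, single uncorrected test; N = 60 gives about 91% for this effect, and 80% power for r of about 0.35.* Add that the planned false discovery rate correction lowers this power. State the number of correlations and, if a figure is given, present the strictest-step value as a floor (for r = 0.40 and N = 60, about 86%, 69% or 55% with 2, 9 or 27 tests).
- **If d was meant:** withdraw N = 44 as the basis for 80% power and state the power at N = 60 as about 33%.
- **In either case:** name the G*Power test and its sidedness.

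The cost is the wording of one paragraph, and possibly a less favourable stated figure. No participants are added and no analysis changes, because the total of 60 rests on direction-dependence analysis and not on this step.

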## Interrelation between sleep, depressive symptoms and psychophysiological correlates

When examining the link between sleep quality, depressive symptoms and psychophysiological correlates, the interrelations are multifactorial and the direction is partially unclear. Fang et al found that the association between sleep and depressive symptoms in adult patients with depression is bidirectional, with sleep impairment being a comorbidity as well as a prodromal sign of a depressive disorder.^26^ In adolescent patients, previous studies reported a connection between sleep problems and later depressive symptoms,^27^ but prior research also identified that higher severity of depressive symptoms was associated with poorer sleep quality.^28^

There are also indications that sleep and stress biomarkers are linked bidirectionally. A hyperactivity of the HPA axis can influence sleep architecture and decrease sleep quality, but sleep impairments also negatively affect functioning of the HPA axis.^29^ A previous study observed a positive association between sleep duration and levels of cortisol, but no association between subjective sleep quality and cortisol levels at awakening, whereas levels of alpha-amylase at awakening were not significantly associated with sleep duration, but a worse subjective sleep quality was associated with higher alpha-amylase levels at awakening.^30^

Much research was performed examining the relationship between cortisol and depressive symptoms in adolescents and adults. In this context, the release of cortisol is considered a heritable trait,^31^ with a connection to current^14^ and future^16^ depressive symptoms. Referring to alpha-amylase, prior research found elevated alpha-amylase levels at awakening in adult patients with depression,^23^ but first investigations in an adolescent sample did not confirm this alpha-amylase morning elevation in adolescent patients with depression.^24^

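### N = 60 rests on a direction dependence analysis that has no calculation behind it, and recruitment at both ends of depression largely sets the distribution shape that the analysis reads

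*Protocol article*

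**What the plan says.** The section A priori power calculation gives three sample sizes. The repeated measures ANCOVA of the cortisol awakening response needs 28 and the correlation between sleep quality and depressive symptoms needs 44, each for 80% power. The total then becomes 60 "to enable the calculation of a direction-dependence analysis in case of non-normally distributed and sufficiently skewed data", made up of "30 participants with a depressive disorder and 30 healthy participants as parallel controls". The first two sizes come with an effect size and a power. The third has neither.

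The section Statistical analysis places the method last and makes it conditional on non-normal, sufficiently skewed outcome variables. In that case "the direction of the relationship between sleep quality and depressive symptoms will be examined with direction dependence analysis". It adds that the method can adjust for covariates, but names none and does not mention group.

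The eligibility sections fix the sampling. Cases must have a diagnosed depressive disorder. Controls are excluded for any psychiatric disease, symptoms pointing to one, past psychotherapeutic or psychiatric intervention, or a need for therapeutic support.

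**The concern.** Direction dependence analysis compares two regressions, sleep on depression and depression on sleep, and uses non-normality of the variables and residuals to decide which way round is plausible. This needs distribution shapes that reflect the process generating the data.

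Here one of the two variables is the one on which people were recruited. The pooled depression score is a mixture of a diagnosed group and a screened-healthy group in a ratio the investigators chose. Its skewness or bimodality, and the residual shapes that follow, depend on that choice. The skewness condition for running the analysis is checked on the same score, so it offers no protection.

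Two things are at stake. A statement about direction could be reported that partly reflects recruitment. And the final sample size is attributed to an analysis for which 60 was never shown to be enough.

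**Working it through.** **1. The stated sample sizes.**
- N = 44 reproduces as a two-sided test of a correlation of 0.40 at alpha 0.05. The noncentrality is 0.40/√(1 − 0.40²) × √44 = 0.436 × 6.633 = 2.90, and 44 is the smallest N reaching 80% power. Fisher's z gives 47. The text labels the effect Cohen's d ("we assume a medium effect size of *d* = 0.40 for correlational analyses of sleep quality and depressive symptoms"); a d of 0.40 would need about 198-203.
- N = 28 depends on unstated settings. With f = 0.30, three measurements and correlation 0.5, the group-by-time test needs 20; a correlation of 0.3 gives 28. The between-group effect would need 62.
- N = 60 has no inputs and cannot be recomputed.

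**2. Skewness of a 50:50 mixture.** For two normal groups with mean difference D and SDs s1 (cases) and s2 (controls), skewness = 0.75·D·(s1² − s2²)/v^1.5, where v = (s1² + s2²)/2 + D²/4. The depression means and SDs below are assumed.
- 28 (SD 8) v 5 (SD 8): s1² − s2² = 0, so skewness is 0 and the mixture is bimodal.
- 25 (SD 8) v 5 (SD 5): v = 44.5 + 100 = 144.5; 0.75 × 20 × 39/144.5^1.5 = 0.34.
- 28 (SD 10) v 5 (SD 4): v = 58 + 132.25 = 190.25; 0.75 × 23 × 84/190.25^1.5 = 0.55.

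The value thus depends on the two group SDs and the ratio. In simulation with a skewed score, changing only the number of cases among 60 (15, 30, 45) gave mean skewness 1.34, 0.52 and 0.01 under one assumed shape, and 1.14, 0.36 and −0.22 under another.

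**3. Effect on the direction call.** Assumptions, none from the article: the causal variable is gamma-distributed; path 0.40; cases are the top 12% on depression; controls lie below the 70th percentile (setting 2 also tried other cut-offs, from the lower 50% to the lower 88%). A direction is declared when the residuals of one model pass a skewness test at 0.05 and those of the reverse model fail it. The settings use different shapes for the gamma variable.

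| True direction | Setting | Random sample of 60 | 30:30 sample |
|---|---|---|---|
| Depression to sleep | 1 | 65% correct | 6% |
| | 2 | 74% | 7-9% |
| | 3 | 81% | 11% |
| Sleep to depression | 1 | 63% | 61% |
| | 2 | 74% | 59-69% |
| | 3 | 83% | 73% |

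The design nearly erases one true direction and largely keeps the other.

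**4. False calls.**
- Bivariate normal data, where no direction is identifiable: random sampling gives depression-to-sleep in 4-5% of runs with the skewness test. At 30:30 the skewness test gives 1-15% depending on the variant, Shapiro-Wilk 16% and a kurtosis test 22%.
- Diagnosis as the only link between sleep and depression, scores 28 (SD 10) v 5 (SD 4-5): depression-to-sleep in 17-31% with the skewness test and 43-85% with Shapiro-Wilk. With equal SDs of 8, the skewness test gives under 1%.

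**5. Two apparent repairs.**
- Group as a covariate: with no identifiable direction, false depression-to-sleep calls are 26% with the skewness test and about 29% with Shapiro-Wilk.
- Cases only (n = 30): truncation at the case threshold gives false depression-to-sleep calls in 52-62% of runs with no identifiable direction.

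**6. What 60 gives for a group comparison.** For 30 v 30, two-sided 0.05 and 80% power, the normal approximation is (1.960 + 0.842) × √(2/30) = 0.72; the noncentral t gives 0.736.

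**The case against.** The best defence is that the analysis is modest in the plan. It is conditional and comes last. Direction is in no hypothesis and is not named in either outcome section; the secondary outcome covers the relation between depressive symptoms and sleep, not which way it runs. N = 60 exceeds both computed sizes, so removing the analysis leaves no stated calculation short. The article does not fix whether the run is pooled, within group or group-adjusted, and a condensed article may leave that to the full protocol. All of this stands, and it limits the severity. It does not remove the point: the method, the variable pair, the quota and the reason for 60 are all stated, and tying the total of 60 to this analysis implies a pooled run.

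A reader might go further in three ways that the documents do not support.
- **That 30:30 recruitment creates the skewness the method reads.** With equal group SDs it creates none, and in most simulated settings it reduced real skewness. Selection can create, reduce or reverse skewness, or produce two modes.
- **That the result is simply invalid and a wrong direction would be published.** With the skewness test, wrong-direction calls in the pooled simulations with a true depression-to-sleep effect stayed near 5%. When a significant skewness test on either variable was also required (an assumed threshold, since the article gives none), only 10-55% of 30:30 samples went forward and wrong calls fell to 1-2.5% of all runs. Under that test the main harm is lost, lopsided detection.
- **That the background contradicts the analysis.** It reports that "the association between sleep and depressive symptoms in adult patients with depression is bidirectional", but this is one cited study in adults. The same section calls the direction partly unclear and describes adolescent evidence both ways, which is a reason to ask the question.

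**Conclusion.** The point holds in a limited form. Nothing in the article supports 60 as the number needed for direction dependence analysis. Because sampling on depression at both ends shapes the distributions the method reads, neither a declared direction nor a failure to find one from the pooled sample can be taken as the population causal direction.

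The size of the effect rests on the assumed score shapes, case and control cut-offs, path of 0.40 and decision rule. Across further score shapes, correct depression-to-sleep calls at 30:30 ranged from 3% to 29%. The asymmetry appeared in all three tabulated settings; the false-call rate varied widely with the normality test and the group SDs. This is a should-fix item, because the analysis is conditional and is not itself named as a primary or secondary outcome.

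**What to change.** - In A priori power calculation, remove direction dependence analysis as the reason for 60. Describe the total by what it gives the primary group comparison: with 30 v 30, 80% power for d of about 0.74 at two-sided 0.05, for a single comparison without covariates or multiplicity correction.
- In Statistical analysis, drop the method. If it is kept, label it exploratory, make no causal-direction claim, and state that participants were selected on depression in a fixed ratio, which shapes the distributions being tested.
- Do not replace it with a cases-only run, and do not present group adjustment as a remedy.

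The cost is a change of wording and, at most, the loss of one conditional exploratory analysis. Recruitment, measurements and the main analyses are unaffected.
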